## Background

Regular administration of immunosuppressants is critical in kidney transplant recipients (KTRs) to reduce the risk of acute rejection and enhance graft survival. A previous study has reported that the major cause of graft loss is antibody-mediated rejection which was shown to be associated with impaired adherence to immunosuppressants [1]. Non-adherence is not only medically significant, being responsible for acute rejection [2, 3] and graft loss [4], but also has wide socioeconomic implications resulting from increased healthcare costs [5] for additional hospitalization, acute rejection treatment, and re-dialysis. Given the multifaceted risk associated with immunosuppression non-adherence in KTRs, aggressive intervention by healthcare professionals to ensure adherence is imperative.

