## Methods/design

### Study objectives

Assuming unintended forgetfulness of KTRs to take immunosuppressants oftentimes, the study seeks to identify how continuous adherence management with the ICT-based centralized clinical trial monitoring system affects drug adherence and how improved adherence is associated with therapeutic drug concentrations as well as immunological and clinical outcomes. It also aims to determine patient satisfaction with the ICT-based centralized monitoring system as well as its stability and cost-effectiveness.

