### Study design

This study has a multicenter, open-label, prospective, randomized controlled trial (RCT) design. One hundred fourteen KTRs who fill out the Informed Consent Form are registered and randomized 1:1 into the ICT-based centralized clinical trial monitoring group (*n* = 57) or the ambulatory follow-up group (*n* = 57). The planned follow-up duration is 6 months (Fig. 1). The ICT-based centralized clinical trial monitoring group is given a smart pill box equipped with a personal identification system. Fingerprint registration is required in advance, so that it would be used for authentication before each use of the smart pill box later. The adherence-related information obtained from the pill box is saved, monitored, and sent out via a home monitoring system. Of the home monitoring system data, those necessary for the clinical trial are extracted and incorporated into the electronic Case Report Form (eCRF) system. All data is consolidated and managed within the comprehensive clinical trial management system (CTMS). In the ICT-based, centralized clinical trial monitoring group, feedback is sent to both patients and medical staff in the form of texts and pill box alarms if there is a dosage/dosing time error or a missed dose.

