Cost-effectiveness evaluation parameters include installation of the ICT-based centralized monitoring system, additional hospitalization due to non-adherence, ambulatory tests, and trips for hospital visits. The expenses of the ICT-based centralized monitoring system will consist of the price of the pill box itself, and the costs for transferring medication use information to the home monitoring system and the eCRF system. In cases in which patients develop acute adverse reactions due to irregular medication use and are hospitalized, receipts of the hospitalization fee, outpatient clinic visit fees, and transportation fees will be collected. We will compare differences in the ICT-based centralized monitoring system expenses, additional hospitalization fees, outpatient clinic examination fees, and transportation fees between the two groups.

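### Cost-effectiveness is an aim and a secondary outcome, but the stated analysis compares cost items only and links no effect to them

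*Protocol article*

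**What the plan says.** All references are to the protocol article.

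- **Study objectives** sets the aim: "It also aims to determine patient satisfaction with the ICT-based centralized monitoring system as well as its stability and cost-effectiveness". Secondary outcomes lists cost-effectiveness again.
- **Secondary outcomes** then says what the evaluation contains: "Cost-effectiveness evaluation parameters include installation of the ICT-based centralized monitoring system, additional hospitalization due to non-adherence, ambulatory tests, and trips for hospital visits". Every entry is a cost.
- It costs the system as follows: "The expenses of the ICT-based centralized monitoring system will consist of the price of the pill box itself", together with the cost of passing medication data to the home monitoring and eCRF systems. It does not say how the price is allocated to the trial period.
- Receipts are described for a subset of patients: "In cases in which patients develop acute adverse reactions due to irregular medication use and are hospitalized, receipts of the hospitalization fee", and likewise for clinic visits and transport.
- The analysis is one sentence: "We will compare differences in the ICT-based centralized monitoring system expenses, additional hospitalization fees, outpatient clinic examination fees, and transportation fees between the two groups".
- **Study design** gives the window: "The planned follow-up duration is 6 months". Only the ICT group receives a pill box.
- Effects are defined elsewhere and measured in both arms: adherence under Primary outcomes, rejection and graft loss under Secondary outcomes. Process evaluation equates effectiveness with improved adherence, but only within the RE-AIM framework. None of these is joined to the costs.

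**The concern.** A cost-effectiveness question asks what is paid for what is gained. The stated comparison supplies only the first half. If the ICT arm costs more and adherence improves, a list of fee differences cannot say whether the gain was worth the money, yet it would be reported under a label that implies it can.

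The itemised comparison has a second weakness. Control patients have no pill box, so the between-group difference in system expense is fixed by the design. As a separate comparison it tells the reader nothing; it matters only as one term in a total.

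At stake is a declared secondary objective that may go unanswered although the trial collects effect data in both arms.

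**Working it through.** **1. Is there a figure to reproduce?** Not for this outcome: the article gives no price, unit cost, event rate or cost difference. Its dropout arithmetic does reproduce (51 / (1 − 0.10) = 56.7, rounded up to 57 per group), but that concerns dose-taking compliance and has no bearing on costs.

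**2. What the stated comparison yields.** Write the difference in mean cost (ICT minus control) as

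ΔC = ΔC(system) + ΔC(hospital) + ΔC(outpatient) + ΔC(transport).

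By design ΔC(system) = mean system expense in the ICT arm − 0, which is positive. The other three terms can take either sign. ΔC is negative only if savings on those three exceed the system expense. The article gives no figures for any term, so the sign of ΔC cannot be derived.

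**3. What the aim needs.** Let ΔE be the difference in effect (ICT minus control).

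- ICT cheaper and no less effective: the system is favoured without a ratio.
- ICT dearer and no more effective: the system is not favoured, again without a ratio.
- ICT dearer and more effective, or cheaper and less effective: ΔC and ΔE must be weighed together.

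Even the first two cases require ΔE to be read beside ΔC, and the stated comparison does not include it.

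**4. How far one cost difference can stretch.** Assume ΔC = 100 units per patient (illustrative). Cost per percentage point of adherence gained = ΔC / ΔE:

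| Assumed gain ΔE (points) | ΔC / ΔE |
|---|---|
| 2 | 100 / 2 = 50 |
| 5 | 100 / 5 = 20 |
| 10 | 100 / 10 = 10 |

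The same cost result fits a five-fold range of cost per point. The ratio also grows without limit as ΔE approaches zero.

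**5. Why the allocation of the box price needs stating.** With straight-line spreading over an assumed life of L years, the share of the price falling in the 24-week window is (24/52) / L:

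| Assumed life L (years) | Share of price |
|---|---|
| 1 | 46% |
| 2 | 23% |
| 3 | 15% |
| 5 | 9% |

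Charged in full, the share is 100%. The article names no rule and no service life, so ΔC(system) is undetermined within this range.

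**The case against.** The strongest reply is that a journal article condenses a fuller document. The choice of ratio, the interval method and the amortisation of equipment commonly sit in an analysis plan, and the parameter list is worded as open. That stands for the technical detail, and the absence of such detail is not the point. But the article goes further than announcing an evaluation: it names the parameters and the comparison, and these do not match the stated objective.

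It can also be said that the trial does measure effects, so a reader could set costs beside adherence. That is correct, and it means the remedy is a link rather than new effect data.

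Three stronger readings are tempting and are not supported:

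- *The full box price is charged to 6 months.* A reader might infer this, but the article only names the price as a component. Any multiple by which device cost is overstated would rest on an assumed service life on top of an assumed charging rule.
- *The ICT arm will almost certainly cost more.* The Background cites savings from avoiding "increased healthcare costs [5] for additional hospitalization, acute rejection treatment, and re-dialysis", and one might expect few such events in 6 months. The article gives no event rates or prices, and it counts hospitalisation due to non-adherence as a possible offset.
- *The evaluation can never answer the question, or applies a wrong test.* A cheaper and no less effective ICT arm would answer it. The sentence speaks of comparing and names no test.

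Two cautions about the remedy also stand. The compliance items are taken from the box in one arm and the diary in the other, so a ratio built on them would inherit that measurement difference. No value per adherence point is stated, so a cost per point informs a judgement but does not make it.

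**Conclusion.** The point holds as a mismatch between objective and analysis. Cost-effectiveness is declared as an aim and a secondary outcome. The analysis specified for it is a set of cost differences with no effect attached, one of which is fixed by design. Unless the ICT arm is both cheaper and no less effective, that comparison cannot show the system to be cost-effective.

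The size cannot be computed from the article. The five-fold range in cost per point and the 9% to 100% range in the share of the box price rest on assumed gains, an assumed cost difference and assumed service lives. They show why the missing link matters; they do not estimate an error. The matter is confined to a secondary outcome: the primary analysis and the sample size of 57 per group are untouched.

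**What to change.** 1. Combine the cost items into one incremental cost per patient over 24 weeks. Show system expense as a line within that total, not as a separate between-group comparison.
2. Report it jointly with an incremental effect measured the same way in both arms. Dose-taking compliance from the pill counts, which Primary outcomes schedules in both groups from week 4 to week 24, is one candidate.
3. Resample patients within arm, keeping each patient's cost and effect together, and give a bootstrap interval for the joint cost and effect difference. Also show the two differences separately, because the ratio is unstable if the adherence gain is near zero.
4. State how the box price is allocated to the 6 months and vary it in a sensitivity analysis, including the full price.
5. Limit the conclusion to 6 months and to the costs captured. Say how patients without receipts enter the total, since receipts are described only for hospitalised cases.

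If this is not wanted, rename the outcome a cost comparison and adjust the objective.

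The cost is a change of wording and a modest analysis, using effect data already planned. The downside is small: an allocation assumption has to be stated and defended.

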### Process evaluation

The Reach, Effectiveness, Adoption, Implementation, and Maintenance (RE-AIM) framework [16] will be used in order to evaluate translatability and feasibility of ICT-based centralized monitoring system. Reach is defined as the absolute number and participation rate of eligible KTRs who participate in the ICT-based RCT. Effectiveness is defined as the improvement in adherence to immunosuppressive medication in KTRs. Adoption is defined as the absolute number, proportion, and representativeness of hospitals that are willing to participate in the ICT-based RCT. Implementation is defined as the percentage of KTRs who follow the ICT-based centralized monitoring system as intended. Maintenance is defined as the extent to which the ICT-based centralized monitoring system became part of the standard monitoring system of adherence to immunosuppressive medication in KTRs.

### System data security

All personal medical records entered in the smart pill box, drug administration management platform, the home monitoring system, the eCRF system, and the comprehensive CTMS are securely protected by means of access control and authentication, automatic user log-off, data encryption/decryption, and system log records for data audit. All systems used in the study adopt personal identifiers (ID and passwords) to ensure that different users (administrators, investigators, and subjects) are given different levels of access to data. Access is restricted if authentication expires.

A pre-defined length of inactivity results in an automatic user log-off and session end. The security measures apply to all hardware and software that collect (generate), access, store, transmit, and process any personal medical information in the home monitoring environment. The personal data (patient data, authentication data, etc.) are encrypted/decrypted when transmitted and stored by security protocols such as SEED, IPsec, SSL, and WAP. When a user obtains access, system log records are generated to track user activities including log-in/log-off, access to data, and creation/update/deletion of data. In case of any illegal access by external intruders to the information system, or of unauthorized activity by insiders, the person in charge of clinical data management should immediately report to the system manager who, if faced with risk of critical information leakage to unauthorized parties, should notify the principal investigator.

### Discontinuation/dropout criteria

A trial subject might discontinue/drop out from the trial if deemed necessary by self or by investigators in accordance with the following criteria:Inappropriate registration: violation of the inclusion/exclusion criteriaLoss of the transplant organRequest by a subject or their legal representative for discontinuation within the trial periodWithdrawal of consent to trial participation by a subjectA subject lost to follow-upOther cases in which continuation of the trial is deemed not appropriate by investigators

### Statistical analysis

For categorical data, percent (%) is used for the number of subjects in a category against the total number of subjects. Analysis of categorical data uses the chi-square test or Fisher’s exact test. For continuous data, descriptive statistics (mean and standard deviation (SD)) are given, and the *t* test and the Mann-Whitney *U* test are used for analysis of normal distribution data and non-normal distribution data, respectively. The inter-group difference in adherence to immunosuppressants is assessed with the *t* test. Summary statistics of mean, SD, median, minimum value, and maximum value are presented for measurement data at each visit. The intra-group variation is analyzed with the paired *t* test or Wilcoxon’s signed rank test. Multivariate analysis is performed to identify clinical factors associated with drug compliance. Statistical significance is obtained with a *P* value of < 0.05.

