### Secondary outcomes

The secondary outcomes in this trial include blood drug levels, immunological outcome, clinical outcome, patient satisfaction with the system, and the system stability and cost-effectiveness. The trough levels of tacrolimus and mycophenolic acid, creatinine level, and eGFR are measured at 4, 8, 12, 16, 20, and 24 weeks of follow-up. PRA is assessed at baseline and 24 weeks, and serum BK virus at 12 weeks. For clinical outcome evaluation, biopsy-proven acute rejection (BPAR) and graft loss developing during the follow-up are monitored. The patient Satisfaction Questionnaire is filled out at 4 and 24 weeks in the ICT-based centralized clinical trial monitoring group in order to assess how well the patients are satisfied with the system-enabled adherence management. The malfunction rate of the ICT-based centralized monitoring system is checked as well as any discrepancy between the smart pill box record and the patient-kept drug administration diary. Information about patients’ medication use sent to the ICT-based monitoring system is compared with the daily records of medication use written by the patients (type of medications used, number of pills ingested, and time of ingestion) to assess how closely they match. Stability is measured by using the following equation:$$ \frac{\mathrm{Number}\  \mathrm{of}\  \mathrm{pills}\  \mathrm{taken}\  \mathrm{over}\ \mathrm{a}\ \mathrm{certain}\  \mathrm{period}\  \mathrm{according}\  \mathrm{to}\  \mathrm{the}\ \mathrm{ICT}\hbox{-} \mathrm{based}\  \mathrm{centralized}\  \mathrm{monitoring}\  \mathrm{system}}{\mathrm{Number}\  \mathrm{of}\  \mathrm{pills}\  \mathrm{prescribed}\  \mathrm{over}\  \mathrm{the}\  \mathrm{sampling}\  \mathrm{period}\  \mathrm{according}\  \mathrm{to}\  \mathrm{the}\  \mathrm{daily}\  \mathrm{record}\  \mathrm{of}\  \mathrm{medication}\ \mathrm{use}}\times 100\%. $$

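### The only test rule for continuous data sends skewed, zero-heavy costs to the Mann-Whitney test, which does not compare mean cost

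*Protocol article*

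**What the plan says.** All references are to the protocol article; no SAP is shown.

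- **Status of the outcome.** Secondary outcomes lists "patient satisfaction with the system, and the system stability and cost-effectiveness".
- **ICT cost.** The same section says "The expenses of the ICT-based centralized monitoring system will consist of the price of the pill box itself", together with the cost of data transfer. Every ICT patient incurs this and no control does.
- **Event-driven cost.** For patients hospitalised after irregular medication use, "receipts of the hospitalization fee, outpatient clinic visit fees, and transportation fees will be collected".
- **Planned comparison.** "We will compare differences in the ICT-based centralized monitoring system expenses, additional hospitalization fees, outpatient clinic examination fees, and transportation fees between the two groups". The section does not say whether the items are summed per patient or compared one by one, and it names no test.
- **Test rule.** Statistical analysis says that for continuous data the t test and the Mann-Whitney U "test are used for analysis of normal distribution data and non-normal distribution data, respectively". Mean and SD are given as descriptive statistics. One outcome has its own between-group test: "The inter-group difference in adherence to immunosuppressants is assessed with the" t test. Costs have none. The significance threshold is P < 0.05, with sidedness not stated there.

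**The concern.** Cost is continuous, a between-arm comparison is promised, and the general rule has no exception for it. On the receipt sentence as written, most controls have zero cost, a few have a large one, and every ICT patient carries at least the device cost. Such data would fail a normality check, so the rule selects Mann-Whitney.

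Mann-Whitney asks how often a randomly chosen ICT patient has a higher cost than a randomly chosen control. It takes almost no account of how much higher or lower. A payer's question turns on mean cost, because mean times number of patients is the bill. If the system saves money, it does so by avoiding a few expensive admissions, and ranking discards the size of those admissions. At stake is a significance statement on cost that does not answer the cost question and, for a combined cost, can point the wrong way.

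**Working it through.** **Inputs from the article.** 51 evaluable per arm, reproduced from the dropout step: 51 / 0.90 = 56.7, rounded up to the stated 57. Test rule and cost structure are as described above. The article states no cost figure, so there is none to reproduce.

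**Assumptions.** Cost unit = one box price. Admission costs and rates are assumed. Tests are two-sided at 0.05.

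**Example A, combined cost.** Admission = 40 units; 12 control and 1 ICT admissions.
- Control mean = 12 × 40 / 51 = 9.41. ICT mean = 1 + 1 × 40 / 51 = 1.78. Difference, ICT minus control = −7.63; percentile bootstrap 95% CI about −12.3 to −2.9.
- Ranks: the 50 ICT patients at cost 1 exceed the 39 controls at 0, and the one at 41 exceeds all 51 controls. Pairs with ICT higher = 50 × 39 + 51 = 2001 of 51 × 51 = 2601, so P(ICT > control) = 0.77 and Mann-Whitney P = 2.5e-7.
- The means show ICT cheaper with an interval excluding zero, while the rank test significantly shows ICT dearer.

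**Example B, combined cost.** Admission = 20 units; 6 control and 2 ICT admissions.
- Control mean = 6 × 20 / 51 = 2.35. ICT mean = 1 + 2 × 20 / 51 = 1.78. Bootstrap CI −2.5 to +1.4, inconclusive.
- Pairs with ICT higher = 49 × 45 + 2 × 51 = 2307 of 2601, or 0.89; Mann-Whitney P = 5.8e-14 for ICT dearer.

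**Same examples, hospitalisation fees alone** (ties counted as one half).
- A: (1 × 39 + ½ × (50 × 39 + 1 × 12)) / 2601 = 1020 / 2601 = 0.39, P = 0.0012. ICT ranks cheaper, in line with mean fees of 0.78 against 9.41.
- B: (2 × 45 + ½ × (49 × 45 + 2 × 6)) / 2601 = 1198.5 / 2601 = 0.46, P = 0.14, again in the direction of the means (0.78 against 2.35).
- No reversal occurs item by item.

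**How often, and when it fades.** Simulated combined cost, 51 per arm: admission 20 units, risk 12% control and 4% ICT, so the true saving is 20 × (0.12 − 0.04) − 1 = 0.6 units per patient. A log-normal routine cost is added in both arms. Share of trials in which Mann-Whitney declares ICT significantly dearer:

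| Mean routine cost (box prices) | CV 0.5 | CV 1 |
|---|---|---|
| 0 | 100% | 100% |
| 2 | about 97% | about 80% |
| 4 | about 46% | about 26% |
| 6 | about 19% | about 11% |
| 10 | about 4% to 6% | about 4% |

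(Repeat runs differ by up to about 3 percentage points.)

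**Second set of assumptions.** Mean admission cost 100 (log-normal, CV 1), device 5, admission risk 20% against 5%, true saving 100 × 0.15 − 5 = 10. ICT is declared dearer in 99.9–100% of runs with no routine cost, 76–82% at routine cost 10, 17–20% at 20 and about 2% at 50. With admission risk 60% against 10% and no routine cost the figure is under 1%. Across all scenarios run, a Welch comparison of means declared ICT dearer in at most 1.7% of runs.

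**The case against.** The strongest reply is that the reversal needs a variable the article does not define. Secondary outcomes lists cost items and never says they are added up per patient. Tested separately, hospitalisation fees did not reverse in either example, and the ICT-expense item is truly higher in the ICT arm. This stands, and the reversal is therefore conditional on combining costs. Item-by-item testing still serves poorly: the ICT-expense item is zero in controls by definition, so its P value says nothing, and ranking the fee items discards their size.

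Second, Statistical analysis does not mention costs, and an unseen SAP or economic plan may set another method. That is possible. But the article states a rule for all continuous data and makes an exception only for adherence, so the point concerns a stated rule and not an omitted detail.

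Third, mean and SD are to be reported, so a reader would see the means beside the rank P value. This softens the problem; the significance statement would still come from ranks.

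Fourth, every price and admission rate here is assumed, and Example A's 12 of 51 against 1 of 51 in six months is a large contrast. A reader might infer that the box price alone decides the test, or that the trial's cost conclusion would be wrong. The documents support neither. Ambulatory tests and trips for visits are listed as cost parameters and both arms attend six visits. If those routine costs are counted for everyone, controls are not mostly at zero and the reversal can largely disappear.

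**Conclusion.** The point holds as a mismatch between test and question. As written, the rule sends skewed costs to a test that does not compare mean cost, whichever way the items are handled.

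A significant result against ICT despite a lower ICT mean is a possibility, not a certainty. It requires costs to be combined per patient and routine costs common to both arms to be small relative to the box price. With a true saving of 0.6 box prices per patient and routine-cost CV 0.5, it occurs in about 97% of simulated trials at a routine cost of 2 box prices, 46% at 4 and 4% at 10. It is also rare when most controls are admitted. These sizes rest on assumed prices, admission rates and two-sided testing, none of which the article supplies for costs.

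The consequence is confined to a secondary outcome. The primary adherence comparison has its own named test and is untouched.

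**What to change.** In Secondary outcomes (cost-effectiveness) and Statistical analysis:

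1. Exempt costs from the normality-based choice of test.
2. Define total cost per randomised patient, including the ICT expense, and say whether outpatient and travel costs enter for all patients or only for those hospitalised.
3. Compare arithmetic mean total cost between arms and give a non-parametric bootstrap 95% CI for the difference.
4. Report the separate items descriptively as means. Apply no rank test to costs and no test at all to the ICT-expense item.

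The cost is a few sentences and slightly more analysis work, with no new data if the total is built from the items already collected. The price is wide intervals: Example B gives −2.5 to +1.4 box prices, which reflects how little a trial of this size can say about mean cost. If the SAP already specifies a mean-cost analysis, a one-line cross-reference is enough.

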### Sample size

We hypothesized that the ICT-based centralized monitoring group would be superior to the control group in terms of dose-taking compliance. A one-tailed test with a 0.05 significance level and 80% power provided a size of 51 in each group. With an estimated 10% dropout, the final sample size of 57 was determined (a total of 114 subjects, 57 in each group).

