### Randomization

Participants who will provide written consent to participate in this clinical trial will be given numbers in the order of their Informed Consent Form submission, and will undergo screening as scheduled. The screening number is a five-digit code. The first digit is the letter S, which stands for “screening.” The second digit contains the institution code, and the last three digits are determined according to the order of consent submission. After selecting appropriate participants based on the inclusion and exclusion criteria, we will give each participant a consecutive participant identification number. The participant identification number consists of five digits. The first digit is the letter R, which stands for randomization. The second digit contains the institution code, and the last three digits are determined according to the order of consent submission. Examinees will apply the participant identification numbers to a randomization table provided by a third-party statistician, and will conduct the medication adherence monitoring method.

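### The primary adherence comparison is fixed as an unadjusted t test; adjusting for centre, age and time since transplant could gain some precision at little cost

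*Protocol article*

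**What the plan says.** The Primary outcomes section makes adherence to medication the primary outcome, and the Sample size section states the hypothesis in terms of dose-taking compliance. The Statistical analysis section first gives general rules for categorical and continuous data, then singles out this comparison: "The inter-group difference in adherence to immunosuppressants is assessed with the" t test. The only model in that section has another stated purpose: "Multivariate analysis is performed to identify clinical factors associated with drug compliance".

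On centres, the Study design section says: "This study has a multicenter, open-label, prospective, randomized controlled trial (RCT) design". In the Randomization section the participant number carries a centre label ("The second digit contains the institution code, and the last three digits are determined according to the order of consent submission"), and allocation works as follows: "Examinees will apply the participant identification numbers to a randomization table provided by a third-party statistician". The section does not mention stratification or blocking. The number of centres is not given.

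The entry criteria under Study participants set a minimum age of 8 years and at least 1 month since transplant, with no upper limit on either. Both must therefore be known before randomisation. In the text, adherence is measured only from week 4 onward.

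**The concern.** A two-sample t test leaves in its error term all variation in compliance between centres and between kinds of patient. The entry criteria admit children and older adults, and patients from 1 month to many years after transplant, so such variation is plausible. The sponsor also plans an analysis to look for clinical factors related to compliance, yet the treatment comparison would use none of them. The trial is planned at 80% power with a one-tailed test, which leaves little margin. If part of the variance can be explained by variables already recorded, the fixed method gives up power and widens the confidence interval for no saving in cost.

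**Working it through.** **Inputs from the Sample size section.** "A one-tailed test with a 0.05 significance level and 80% power provided a size of 51 in each group". The section then allows for 10% dropout and arrives at 57 per arm. No expected difference or SD is stated, so 51 cannot be derived forward.

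**The plan's own figures.** The dropout step reproduces: 51/0.9 = 56.7, rounded up to 57. Solving backward for the standardised difference d that gives 51 per arm:

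d = √(2/51) × (1.645 + 0.842) = 0.492 (normal approximation); 0.496 with the noncentral t distribution.

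**Power after adjustment.** If centre and covariates explain a share R² of the variance, the residual SD is SD × √(1 − R²), and

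power = Φ( d√(51/2) / √(1 − R²) − 1.645 ), with d√(51/2) = 0.492 × 5.05 = 2.486.

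Every R² below is an assumption.

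| R² | SE relative to unadjusted | Power, normal, d = 0.492 | Power, noncentral t, d = 0.50 |
|---|---|---|---|
| 0 | 1.00 | 80.0% | 80.6% |
| 0.05 | 0.975 | 81.8% | 82.3% |
| 0.10 | 0.949 | 83.6% | 84.1% |
| 0.20 | 0.894 | 87.2% | 87.7% |

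Both columns give gains of about 2, 4 and 7 points.

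**Cost in degrees of freedom.** With noncentral t, d = 0.492 and R² = 0, power is 79.5% on the 100 degrees of freedom of the plain t test. It is also 79.5% with one covariate and 2 to 8 centres in the model (98 down to 92 degrees of freedom). The half-point gap from 80.0% comes from using the t distribution instead of the normal, not from adjusting.

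**A cost not in the table.** Each added term that is not balanced by design also inflates the variance of the arm difference through its chance imbalance. The expected factor is about 1 + q/(N − q − 3) for q terms. With N = 102 and q = 3 this is 1 + 3/96 = 1.03. At R² = 0, power would then be Φ(2.486/√1.03 − 1.645) = Φ(0.805) = 79.0%, a loss of about 1 point. The gains in the table shrink similarly, which is a reason to keep the list short.

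**If the table is stratified or blocked by centre (not stated).** A t test that ignores a balanced factor has an SE that is too large. Its true one-sided error is 1 − Φ(1.645/√(1 − R²)): 4.6% if centre explains 5% of the variance, 4.1% if 10% and 3.3% if 20%, against a nominal 5%.

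**The case against.** The strongest reply is that nothing here is wrong. An unadjusted t test is valid under randomisation, and an article may leave covariate lists to an analysis plan that is not shown. The validity point stands. The second point stands only in part: the article does not leave the method open but names a test for this comparison, and an analysis plan that followed it would run that test. The planned multivariate model might include arm, since nothing excludes it, but its stated purpose is to find factors related to compliance.

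Three stronger readings are tempting, and the article does not support them.

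- *Allocation runs within centres, so the test has the wrong size.* The institution code in the participant number does not show this. The screening number has the same format and allocates nobody, so the code may be only a label. The "randomization table provided by a third-party statistician" is not described further. Even if the table were stratified, the test would be conservative, not invalid.
- *Strongly prognostic baseline data are in hand.* No section says that age, time since transplant or centre predicts adherence. The covariate most likely to help, adherence before randomisation, is not recorded in the text, and the schedule figure is not available.
- *Chance imbalance biases the t test.* Under randomisation, such imbalance is random error that the standard error already covers.

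It is also fair to say that adjustment does nothing about adherence being taken from the pill box in one arm and the diary in the other.

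**Conclusion.** The point holds as a recommendation on efficiency. The article fixes the primary comparison as an unadjusted t test and leaves out centre, age and time since transplant, all known before randomisation. The possible gain is about 2 to 7 power points for R² of 0.05 to 0.20, somewhat less after allowing for chance imbalance in the added terms, and nothing or a loss of about 1 point if R² is near 0. The size rests on an assumed R² and on a difference of about 0.49 to 0.50 SD that is back-solved from 51 per arm, because the article gives neither. The conservative error rate applies only if the randomisation table is stratified or blocked by centre, which the text does not say. The change is worth making because it is cheap, but the trial is not invalid without it.

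**What to change.** Before data are examined, specify the primary analysis as a linear model of dose-taking compliance on arm, with centre and a short, pre-named list of baseline covariates: age, time since transplant, and a pre-randomisation adherence score only if one is collected. Report the adjusted mean difference with its confidence interval, and keep the t test as sensitivity analysis. State whether the randomisation table is stratified or blocked by centre; if it is, the centre term should be in the model for that reason as well. If there are many small centres, say in advance how they will be combined.

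The change needs wording only and no new data. It costs a few degrees of freedom and the small variance inflation shown above. Naming the covariates in advance also removes the chance to choose them after seeing results in an open-label trial.
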